## Abstract

**Background:**

Tobacco smoking is a highly prevalent, addictive behaviour and a key public health priority. However available cessation therapies have low quit and high relapse rates, indicating an urgent need for more effective treatments. Predicated on promising preclinical and pilot clinical data, this paper presents a rationale and protocol for the trial of N-acetylcysteine (NAC) as a novel anti-craving smoking cessation aid.

**Methods:**

Current smokers (*n* = 120) of at least 10 cigarettes a day are recruited through online advertisements, print publications and dissemination of flyers. Participants are randomised on a 1:1 ratio to receive either 16-week treatment of 1.8 g/day of NAC or placebo with all participants receiving quit support from the online QuitCoach tool. Participants are attending visits at baseline, 8 and 16 weeks with a 42-week post-discontinuation follow-up. The primary outcome measure is sustained abstinence at six months after treatment based on self-reported rating scales and confirmed by exhaled carbon monoxide and salivary cotinine levels. Secondary outcomes are timing of the first lapse and relapse, between-group cigarette consumption, withdrawal symptoms, general wellbeing and mood/anxiety symptoms. Between-group differences in adverse events and subgroup analyses for variables including gender and Diagnostic Statistics Manual 5 diagnostics will also be investigated.

**Discussion:**

The planned trial addresses an issue of major importance to human health and, if an effect is shown, may result in substantial changes to the management of smoking and nicotine addiction with overt public health implications.

**Trial registration:**

Australian New Zealand Clinical Trials registry (ANZCTR), ACTRN12617001478303. Registered on 19 October 2017.

**Electronic supplementary material:**

The online version of this article (10.1186/s13063-019-3628-5) contains supplementary material, which is available to authorized users.

## Introduction

Tobacco smoking is the leading cause of preventable morbidity and mortality globally [1] and kills > 19,000 people in Australia each year [2], which includes between one-half and two-thirds of all long-term users [3]. While the prevalence rate in the general community has decreased over the past decade, linked to effective public health interventions, the rate of decrease in the prevalence of smoking has been slowing and there remains a substantial core group of persistent smokers.

It is essential to trial new strategies and medications to make further significant gains in reducing tobacco smoking. Developing a safer, better tolerated pharmacotherapy for smoking cessation is a critical step towards making further gains. Vulnerable groups and special populations may especially benefit from a low-cost, over-the-counter, effective pharmacotherapy with a better safety profile than existing pharmacotherapies such as varenicline and bupropion [4–8].

N-acetylcysteine (NAC) has antioxidant properties, both increasing glutathione and modulating glutamatergic, neurotropic, mitochondrial and inflammatory pathways [9]. NAC is a globally available nutraceutical supplement that is well tolerated, with a side effect profile that does not differ significantly from placebo in clinical trials when administered orally at doses up to 3 g/day with the exception of usually mild gastrointestinal side effects [10]. There are data to suggest that it is efficacious for reducing the number of cigarettes smoked [11] and relapse prevention [12]. NAC may also improve some of the physical harms caused by tobacco smoke exposure, improving mucociliary transport [13] and preventing oxidative damage to lung and other tissues [14, 15].

There are four small published pilot studies investigating the effects of NAC in nicotine dependence. A short-term abstinence study of heavy smokers (*n* = 22), treated for 3.5 days with NAC (3.6 g/day) or placebo, identified that NAC-treated participants reported that their first cigarette was significantly less rewarding when compared with the first cigarette of placebo-treated smokers [12]. A four-week, open-labelled study of tobacco smokers (*n* = 19) treated with NAC and varenicline reported a reduction in cigarettes smoked per day [16]. A randomised trial reports that after four weeks of 2.4 g/day of NAC treatment (*n* = 33, compared with placebo), there was a significant decrease in the number of cigarettes smoked, but no reduction in craving, withdrawal symptoms or level of carbon monoxide.

In another pilot trial, participants were randomised to 12 weeks of 3 g/day NAC (*n* = 17) or placebo (*n* = 17) adjunctive to addiction-focused cognitive behavioural therapy. NAC treatment significantly reduced the number of cigarettes smoked daily, exhaled carbon monoxide and improved depression scores. Quit rates were 47.1% in those treated with NAC versus 21.4% of placebo-treated patients. There were no significant differences in treatment emergent adverse events (AEs) between both groups. These pilot data are very promising [17] and suggest the need for larger more definitive trials of NAC for smoking cessation.

### Study aims and hypotheses

The aim of this study is to investigate the efficacy of NAC (1.8 g/day) for smoking cessation in a randomised, placebo-controlled trial of current smokers who wish to quit smoking. The primary outcome measure will be 24 weeks of continuous abstinence from end of treatment (EoT; 16 weeks) in tobacco smoking, confirmed by biological measures. Secondary outcome measures include point prevalence abstinence, time to relapse and total cigarette consumption. Safety, tolerability and subgroup analyses will also be conducted.

It is hypothesised that: (1) treatment with NAC will be superior to placebo for smoking cessation at follow-up (week 42), confirmed by assaying exhaled carbon monoxide, salivary cotinine (COT); and (2) treatment with NAC will be superior to placebo for smoking cessation at treatment endpoint (week 16), confirmed by assaying exhaled carbon monoxide, salivary COT.

## Methods

### Overview

This is a double-blind, randomised, placebo-controlled trial, to compare 1.8 g/day of NAC with placebo for smoking cessation, conducted over a period of 16 weeks. A six-month post-treatment discontinuation (week 42) follow-up is assessing ongoing abstinence. Data are collected by interview at baseline and weeks 8 and 16, and at the follow-up visit, six months after completion of the trial or 42 weeks in total. The trial has approval from the relevant research and ethics committees and is being conducted in accordance with the Good Clinical Practice (GCP), Australian Clinical Trial guidelines and the National Ethical guidelines for Human Research. The trial is registered on the Australian New Zealand Clinical Trials registry (ANZCTR), ACTRN12617001478303. This study was approved by the Barwon Health Human Research Ethics Committee (reference: 17/15).

The study is being conducted at two sites, Barwon Health, Geelong and the Deakin University Burwood campus. Participants (*n* = 120) are randomised to 16 weeks of treatment with NAC (1.8 g/day) or placebo effervescent tablets taken with water. The first participant was recruited in November 2017 and recruitment is ongoing. The study is being sponsored by Barwon Health and is supported by the ARC Harry Windsor Research Grants Scheme 2017.

### Inclusion and exclusion criteria

Participants are required to meet the following criteria: currently planning to quit tobacco smoking and set a quit date no more than one week from the proposed trial commencement date; aged ≥ 18 years; capacity to consent to the study and to follow its instructions and procedures; current daily smoker of ≥ 10 cigarettes per day. Participants are ineligible to enter the trial under the following conditions: known or suspected clinically unstable systemic medical or psychiatric disorders that require acute medical treatment; current use of oral glucocorticoids; active gastrointestinal ulcers; pregnancy or breastfeeding, or planning a pregnancy within six months; current use of > 500 mg NAC/day; a history of anaphylactic reaction to NAC or any component of the preparation. Only one member of a household is permitted to participate in the trial concurrently to minimise cohort-confounding effects. There are no restrictions on bupropion, varenicline or nicotine replacement therapy (NRT) use before the baseline visit. Female participants are required to be utilising effective contraception if of childbearing age and sexually active.

### Withdrawal criteria

Participants are withdrawn from the trial under the following conditions: failure to take the trial medication for seven consecutive days; pregnancy; emergence of serious AEs suspected to be associated with the trial medication; or commencement of a different pharmacotherapy for smoking cessation during the 16-week treatment phase. Participants will be questioned about these events and their adherence to the study protocol at the bi-weekly telephone interviews during the treatment phase of the study. Withdrawal of consent at any time in the study will result in immediate withdrawal from the trial.

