## Variables and instruments

The primary outcome of this aid-to-cessation trial will be between-group differences in continuous abstinence for the 26-week period between weeks 16 and 42. The primary outcome is measured at six months post-treatment discontinuation (week 42) rather than at treatment discontinuation (week 16), in line with the Russell Standard for international smoking cessation research [22]. To assess self-reported smoking habits, participants will complete a timeline followback (TLFB) at each contact visit. This measure has been shown to be accurate up to 12 months before interview [23]. Abstinence from smoking will be measured by self-report, exhaled carbon monoxide (CO_EXH_) < 10 ppm measured using a Micro+ Smokerlyzer (Bedfont Scientific) and salivary COT < 50 ng/L, which is a sufficient margin to allow for passive tobacco smoking. CO_EXH_ may be < 10 ppm in non-abstinent participants who have not smoked within 2 h [24]. Smoking cessation will be confirmed if CO_EXH_ levels are < 10 ppm and COT is < 50 ng/mL. Where participants self-report use of non-tobacco nicotine, CO_EXH_ will be used to confirm abstinence. Secondary outcomes will include the timing of the first lapse and first relapse, based on a dichotomous variable and defined as self-reported smoking seven days in a row at any time between two weeks after quitting and the trial end. Prolonged abstinence will also be reported and defined as any slips or lapses following the quit date [25].

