At the baseline visit, the Fagerström Test for Nicotine Dependence and a smoking history questionnaire will be administered. The smoking history questionnaire will explore how long the participant has smoked for (e.g. age of first use, duration of use), their average consumption of cigarettes and the number of previous attempts to quit smoking. Data will also be collected regarding how determined they are to give up smoking on this attempt (on a Likert scale of 1–4) and to rate their chances of permanently quitting on this attempt (on a Likert scale of 1–6). The Minnesota Nicotine Withdrawal Scale will be administered to assess urge to smoke among other withdrawal symptoms, depressed mood, irritability, anxiety, difficulty concentrating, restlessness, increased appetite and sleep. Participants will also complete the Brief Questionnaire of Smoking Urges, which assesses cravings related to desire to smoke and expectations of positive effects anticipation of relief from negative affect. Demographic data, lifetime history of smoking (e.g. motivation, readiness to quit, previous attempts), level of social support, self-reported medical and psychiatric history will also be collected at baseline. A psychiatric diagnostic interview (SCID-5-RV), based on the DSM-5 will be conducted at baseline. The WHO ASSIST and AUDIT will be collected at baseline and visits at weeks 8 and 42. The Standardised Assessment of Personality – Abbreviated Scale (SAPAS), a brief screen for personality disorder, will be used at baseline. The WHO-5, Depression, Anxiety, and Stress Scale (DASS-21) and K10 will be administered at baseline and at weeks 8, 16 and 42 (Table 1). To optimise retention and adherence with the treatment protocols, telephone contact will be made with each participant once a fortnight beginning one week after baseline. Progress and adherence self-report data will be recorded on a questionnaire at these telephone calls. Participant reports of adverse effects will be recorded, appropriate interventions according to medical assessment will be implemented and AEs will be further monitored. Six months following the final study visit the participant will be contacted and a follow-up questionnaire conducted to assess if participants have continued to smoke, and at what level, since completing the trial. CO_EXH_ and COT measures will be taken.

**Table 1 Tab1:** Summary of measures collected and other activities at each study visit

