	Baseline	8 weeks	16 weeks	42 weeks (follow-up)
Demographic/health questionnaire	X			
Fagerström Test for Nicotine Dependence	X	X	X	X
Lifetime history of smoking	X			
SCID −5-RV	X			
SAPAS	X			
Exhaled CO (CO_EXH_)	X	X	X	X
MNWS	X	X	X	X
QSU-brief	X	X	X	X
Salivary cotinine	X	X	X	X
K10, DASS-21	X	X	X	X
AUDIT	X		X	X
WHO-5	X	X	X	X
WHO ASSIST	X		X	X
TLFB	X	X	X	
Dispensing of study medications	X	X		

Safety and tolerability outcomes will be assessed by comparison of reported AEs for all NAC-treated and placebo-treated participants and for subgroups. Subgroup analyses will be performed for groups categorised by variables including gender and SCID diagnosis. Participants will be considered to have completed the study if they completed all follow-up examinations to week 42. Individuals who never quit or who relapse (defined as smoking on seven consecutive days), will be examined separately as well as pooled as treatment failures. Non-cigarette tobacco use, but not non-tobacco nicotine use, will be categorised as smoking.

Intended use of bupropion, varenicline or NRT during the 42-week trial period will not be permitted but is only a withdrawal criterion if used during the 16-week treatment period. Some participants may decide to use NRT during the 42-week study. Although this is contrary to the directions given to participants in the study, it is not a study withdrawal criterion and these participants may remain in the study. COT levels will be measured using chromatographic techniques.

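### The withdrawal rule does not separate stopping study medication from leaving follow-up; read plainly, it ends outcome collection for participants selected by post-randomisation events

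*Protocol article*

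**What the plan says.** The Withdrawal criteria section lists four triggers. The first two are in "Participants are withdrawn from the trial under the following conditions: failure to take the trial medication for seven consecutive days; pregnancy" and the other two in "emergence of serious AEs suspected to be associated with the trial medication; or commencement of a different pharmacotherapy for smoking cessation during the 16-week treatment". The section then says of consent: "Withdrawal of consent at any time in the study will result in immediate withdrawal from the trial". All five events therefore lead to the same place.

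Variables and instruments returns to the subject after Table 1. Use of bupropion, varenicline or NRT in the 42 weeks "will not be permitted but is only a withdrawal criterion if used during the 16-week treatment period". The same paragraph then says of NRT use during the 42-week study that "it is not a study withdrawal criterion and these participants may remain in the study".

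The primary outcome, in the same section, is continuous abstinence from week 16 to week 42, verified by exhaled CO and salivary cotinine. Treatment ends at week 16. Statistical analysis plans a modified intention-to-treat approach that follows CONSORT.

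**The concern.** Three of the four triggers (a gap in taking tablets, a suspected drug-related serious adverse event, a switch to another cessation drug) arise from how the participant is faring on the allocated treatment. All four occur after randomisation, and none makes abstinence at week 42 unmeasurable. By the outcome window nobody is meant to be taking tablets, so having stopped early is no reason to stop measuring.

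The events are unlikely to be independent of outcome or arm. People who relapse may stop taking tablets, and people struggling to quit may turn to another drug. The Introduction names gastrointestinal effects as the exception to NAC's placebo-like tolerability. If such people leave follow-up, the arms that remain are no longer the arms that were randomised. An analysis plan can assign or impute their outcome, but it cannot supply CO, cotinine or smoking reports that were never taken. The rule on data collection therefore has to be settled in the protocol.

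**Working it through.** **Step 1: what withdrawal means in the text**

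- In the Withdrawal criteria section, the sentence that removes people from the trial uses a separate term, trial medication, for the drug. The plain reading is that more than the drug stops.
- Withdrawal of consent, which does end data collection, is given the identical consequence.
- After Table 1, failing to meet a study withdrawal criterion is what allows a participant to remain in the study. Meeting one is thus set against remaining.
- No section describes assessments after withdrawal, or a status of off tablets but still followed.

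**Step 2: what the rule touches**

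The outcome window is weeks 16 to 42. Adherence and the withdrawal events are asked about in the treatment-phase telephone calls, so a participant can be withdrawn before the window opens. The paragraph after Table 1 pools as treatment failures those who never quit or who relapse. Withdrawn participants are not named there.

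**Step 3: size of the possible bias**

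The plan states no figure for rule-based withdrawal or for bias, so there is none to reproduce. Inputs:

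- Abstinence p, the same in both arms (no true effect): 1%, the planning rate for placebo in Sample size; 8%, which is that 1% plus the 7-point target difference; and 20%, an assumed high value.
- Withdrawn: w_N = 20% on NAC and w_P = 10% on placebo. Both are assumptions.

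Case A: withdrawn people are abstinent at the same rate as others but are counted as smokers. The observed rate is p(1 − w), and the bias is p(1 − w_N) − p(1 − w_P).

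Case B: withdrawn people all smoke but are left out of the analysis. The observed rate is p/(1 − w), and the bias is p/(1 − w_N) − p/(1 − w_P).

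| True rate, both arms | Case A, NAC vs placebo | Bias A | Case B, NAC vs placebo | Bias B |
|---|---|---|---|---|
| 1% | 0.8% vs 0.9% | −0.1 points | 1.25% vs 1.11% | +0.14 points |
| 8% | 6.4% vs 7.2% | −0.8 points | 10.0% vs 8.9% | +1.1 points |
| 20% | 16% vs 18% | −2.0 points | 25% vs 22.2% | +2.8 points |

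With 60 per arm these are at most 0.0014 × 60 = 0.08 participants at 1%, 0.011 × 60 = 0.7 at 8%, and 0.028 × 60 = 1.7 at 20%.

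A wider gap, 30% vs 10% withdrawn at 5% abstinence, gives 3.5% vs 4.5% (−1.0 points) in case A and 7.1% vs 5.6% (+1.6 points) in case B. With 20% withdrawn in both arms at 5%, the rates are 4.0% vs 4.0% or 6.25% vs 6.25%, so there is no bias under no effect. In these scenarios the bias needs unequal withdrawal.

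**Step 4: why analysis alone cannot settle it**

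Swap the two handling rules. If withdrawn people quit at the common rate and are left out, the observed rate is p(1 − w)/(1 − w) = p. If they all smoke and are counted as smokers, it is again p. Each rule is unbiased in one situation and biased in the other. Only follow-up data on withdrawn people can show which situation holds.

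**The case against.** The strongest reply is that non-collection is nowhere stated. This is an article that condenses a protocol not shown here, and that protocol may provide for follow-up after withdrawal. The vocabulary is also mixed. Overview describes a trial conducted over 16 weeks with follow-up after its completion, and Variables and instruments asks about smoking since the trial was completed. In those places the trial is the treatment phase, and withdrawal from it could mean leaving only that phase. Elsewhere the article speaks of a 42-week trial period. This objection stands in part: a reader might take it as established that week-42 data are not collected, and the documents do not go that far. It does not remove the point. The stated rule treats stopping tablets and withdrawing consent alike, and if follow-up is intended the wording needs correcting. The contrast after Table 1 is also weaker evidence than it looks, because the NRT statement there conflicts with the sentence before it.

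Three further inferences are tempting but not supported:

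- **Pregnancy.** A reader might infer that eligibility guards only against pregnancy planned within six months, and that the rule also removes people in the drug-free weeks. The eligibility text, "pregnancy or breastfeeding, or planning a pregnancy within six months", also covers current pregnancy, and the section requires effective contraception. The withdrawal events are asked about at treatment-phase calls; removal after week 16 is not stated.
- **Timing of follow-up.** The sentence "Six months following the final study visit the participant will be contacted and a follow-up questionnaire conducted" might suggest a clock that starts at an early leaver's last visit. Overview fixes follow-up at 42 weeks in total, and Table 1 agrees.
- **Power.** A loss of power could be computed only by assuming that withdrawn people would have quit as often as others. If they are mostly smokers and are counted as such, little power is lost.

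**Conclusion.** The point holds as a defect in a stated rule. Five events share one consequence, four of them are no reason to stop measuring smoking, and on the plain reading the primary outcome is lost selectively. That conflicts with the modified intention-to-treat aim and with an outcome measured off treatment.

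The numerical bias is modest and uncertain. Under the assumed 20% vs 10% withdrawal and no true effect, it is about 0.1 point at the planned placebo rate, about 1 point at 8%, and 2 to 3 points at 20%. It goes against NAC if withdrawn people who in truth quit as often as others are counted as smokers, and in favour of NAC if withdrawn smokers are left out. The withdrawal shares are not in the documents; equal shares would give no bias in these scenarios, and reversing the gap would reverse the signs. At the planned 1% the shift is under a tenth of a participant per arm, so the case for change rests on the avoidable loss of the primary outcome more than on a large expected distortion.

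Separately, the article contradicts itself on whether NRT use in the treatment phase is a withdrawal criterion. Which version applies is not judged here.

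**What to change.** In Withdrawal criteria, leave the listed reasons as they are, but say separately what ends study medication and what ends follow-up. For every reason except withdrawal of consent, state that the participant keeps the scheduled week 8, 16 and 42 smoking assessments (self-report, exhaled CO, cotinine) and is analysed in the randomised arm. If the full protocol already provides this, correct the published wording to match.

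Reconcile the Withdrawal criteria section with the paragraph after Table 1 on NRT use in the 16-week phase, so that one rule is stated.

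The cost is an amendment, which under Study management and governance needs ethics approval, and some extra effort to reach people who have stopped tablets. The assessments are already on the Table 1 schedule. Recruitment was still open when the article was written, so later participants would benefit.
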